## Abstract

This study protocol aims to analyze and compare the effects of combined movement and storytelling intervention (CMSI) on fundamental motor skills (locomotor skills and object control), language development (language comprehension, language expression, vocabulary and language description), and physical activity levels (light intensity, moderate-to-vigorous intensity and sedentary time) in children aged 3 to 6 years. The sample will consist of 144 children from 12 class groups, randomly assigned to 3 experimental groups (*n* = 72 children) and 3 control groups (*n* = 72 children), belonging to 4 class groups of upper-middle-level classes (2 experimental and 2 control; 3 to 4 years), 4 transition level 1 classes (2 experimental and 2 control; 4 to 5 years) and 4 transition level 2 classes (2 experimental and 2 control; 5 to 6 years). The experimental groups will perform CMSI for 3 sessions per week (40 min per session) over 12 weeks (using one motor story per week), while the control groups will not receive any treatment. The main outcome will provide information about fundamental motor skills, language development, and physical activity levels. Our hypothesis indicates that CMSI has the potential to generate significant increases in selected assessments. If this intervention proves to be beneficial, it could contribute to preschool and school curricula.

## 1. Introduction

A physically active lifestyle should begin at an early age and continue throughout the life cycle [1,2], with a synergistic relationship between physical activity and motor competence [3]. The development of fundamental motor skills (FMSs) is a favorable antecedent and significantly related to longer periods of moderate-to-vigorous physical activity (MVPA) in children (*p* < 0.05) [4]. FMSs denote the mastery of common basic motor skills with specific patterns; these can be classified as locomotor, object control, and stability skills, which favor the development of advanced and complex movements that allow participation in high-motor-engagement activities [4]. 

Thus, FMSs represent a key factor for healthy development in early childhood [5,6]. A systematic review conducted by Bolger et al. [7] showed that FMS competence increases with age during childhood, with locomotor skills being greater than object control. In addition, physical inactivity leads to impaired motor competence and correlates negatively with language development (β = −0.664; *p* = 0.004) in children aged 3 to 5 years [8]. Furthermore, Wang et al. [9] indicated that stability for the motor domain within each developmental area is high (motor competence) from 3 to 5 years of age, while unique prediction from one domain to the other is weak.

In this regard, a systematic review by Lin et al. [10] reported that FMS-focused physical activity interventions in children lead to improved postural control, motor competence and muscle strength compared to traditional physical education classes. In a meta-analysis conducted by Van Capelle et al. [11], FMS-focused interventions lasting 17 to 21 weeks with a frequency of 1 to 3 sessions of 17 to 35 min, led by teachers, significantly improved overall FMSs (SMD = 0.14; 95% CI = 0.06 to 0.21; *p* = 0.0003), object control (SMD = 0.47; 95% CI = 0.15 to 0.80; *p* = 0.004) and locomotor skills (SMD = 0.44; 95% CI = 0.16 to 0.73; *p* = 0.002) compared to children aged 3 to 5 years who were given no teacher-led FMS interventions. In another study, Han et al. [12] reported a moderate correlation between FMS scores in executive functions (r = 0.33; *p* < 0.001) and scores in locomotor skills, which were found to be significant predictors of inhibitory control (β = 0.21; *p* < 0.001), working memory (β = 0.18; *p* < 0.01) and cognitive flexibility (β = 0.24, *p* < 0.001) in children aged 3 to 5 years. 

Additionally, a systematic review by Jylänki et al. [13] reported that FMS interventions were effective in improving executive functions, language, arithmetic skills, cognitive skills, and memory in children aged 3 to 7 years; however, these studies presented a low methodological quality. In general, FMS proposals are based on locomotor skills, object control, and stability skills, with less common FMS strategies involving not only motor competence but also relating to motor stories that are used to stimulate the cognitive state of schoolchildren [14]. 

Combined movement and storytelling intervention (CMSI) is emerging as an FMS strategy that has shown significant improvements in motor, cognitive and linguistic skills in children [14,15]. In a study conducted by Eyre et al. [15], involving a non-randomized controlled trial with a 12-week CMSI, significant improvements (*p* ≤ 0.01) were reported in seven motor skills (run, jump, throw, catch, stationary dribble, roll and kick) in South Asian children aged 5 to 6 years. Similarly, Duncan, Cunningham and Eyre [14] conducted a randomized controlled trial over 6 weeks, using CMSI with preschool children in England, and reported significant improvements in motor (Δ 4.86; *p* = 0.001) and language (Δ 13.6; *p* = 0.001) skills compared to two active control groups. 

Taking into account the benefits of promoting FMSs at an early age and considering the dearth of scientific literature to date on novel strategies such as CMSI [14,15], it becomes relevant to analyze the possible changes/benefits of introducing CMSIs to preschool children. Therefore, this study protocol aims to analyze and compare the effects of CMSI on FMSs (locomotor skills and object control), language development (language comprehension, language expression, vocabulary and language description) and physical activity levels (light physical activity, LPA; MVPA; and sedentary behavior, SB)—in children aged 3 to 6 years. Based on previous studies [14,15], it is hypothesized that CMSI has the potential to generate significant increases in locomotor skills, object control, language comprehension, language expression, vocabulary, language description and MVPA level compared to control groups.

## 2. Material and Methods

### 2.1. Study Design

The study is based on a double-blind, repeated measures and parallel groups (6 interventions and 6 controls) (randomized controlled trial) experimental design; considering previous studies, a quantitative approach will be adopted [16]. The methodology followed will be the Consolidated Standards of Reporting Trials Statement (CONSORT) methodology [17]. 

### 2.2. Ethical Approval

The current protocol has been reviewed and approved by the Scientific Ethics Committee of the Universidad Católica del Maule, Chile (approval number: N°105/2021, 4 August 2021) and developed following the Declaration of Helsinki for work with humans. In addition, it has been registered in the Clinical Trial Protocol Registry and Results System (ClinicalTrials.gov (https://clinicaltrials.gov/ct2/home, accessed on 28 August 2022) of the United States of America (code: NCT06016296).

### 2.3. Sample Size Calculation

Twelve children will be recruited from each class group (without gender distinction). The distribution of the class groups (12 class groups) will be in 3 experimental groups (6 class groups, n ± 72 children) and 3 control groups (6 class groups, n ± 72 children). The distribution by clusters or strata is justified by the fact that the use of individual randomization would imply a high probability of contaminating the control groups since it is unfeasible to prohibit children from interacting in school classrooms or recreational spaces (i.e., playgrounds, hallways, laboratories), which is where the study intervention will be carried out [18,19]. In addition, in the Maule region (one of the sixteen regions into which to Chile is divided; located in the center of the country and bordered to the north by the O’Higgins region, to the east by the provinces of Mendoza and Neuquén belonging to Argentina, to the south by the Ñuble region and to the west by the Pacific Ocean), there are 54 educational establishments that provide preschool education with an enrollment of approximately 1080 children. 

The sample size calculation indicates that the ideal number of participants per group is 10. As agreed in a previous study by Eyre et al. [15], we will use a mean difference of 3.22 total score of locomotor skill domains for this calculation as the minimum difference necessary for substantial clinical relevance, with a standard deviation of 0.70 points, considering an alpha level of 0.05 with a power of 80% and an expected loss of 15%. The GPower program (version 3.1.9.6, Franz Faul, Universiät Kiel, Kiel, Germany) will be used to calculate the statistical power. 

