### 2.9. Primary Outcomes

#### 2.9.1. Fundamental Motor Skills (FMSs)

These will be assessed by means of the test of gross motor development-second edition (TGMD-2) [24]. This battery measures 12 FMSs in two different domains (locomotor skills and object control). The locomotor skills domain contains 6 assessments: (i) running, (ii) galloping, (iii) hopping on one foot, (iv) long jumping, (v) horizontal jumping and (vi) lateral sliding. The object control domain also includes 6 assessments: (i) batting a stationary ball, (ii) stationary dribbling, (iii) catching a ball, (iv) kicking a ball, (v) throwing a ball and (vi) rolling a ball. Estimated administration time is ≤10 min per child. The 6 locomotion skills and 6 object control skills incorporate 24 criteria, allowing a total score from 0 to 48 points. The domain scores can be transformed into a standard score (median = 10.0 and standard deviation = 3.0) and subsequently into a gross motor quotient (median = 100.0 and standard deviation = 15.0). This information can be found in percentiles that allow the child to be placed in normative values with respect to a reference population. The original TGMD-2 reports high test–retest and inter-rater reliability (all r values > 0.85), as well as good internal consistency that varies between 0.85 and 0.88 for each ability [24]. In addition, its content, construct and concurrent validity have been demonstrated in children aged ≥ 3 years in countries such as Chile [25,26], Brazil [27] and Korea [28]. 

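### The stated 10 participants per group at 80% power does not follow from the stated inputs, and the calculation makes no allowance for allocation by class

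*Protocol article*

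**What the plan says.** Section 2.3 of the protocol article gives both inputs and result. The difference: "we will use a mean difference of 3.22 total score of locomotor skill domains for this calculation". The spread: "with a standard deviation of 0.70 points". The remaining settings: "considering an alpha level of 0.05 with a power of 80% and an expected loss of 15" per cent. The result: "The sample size calculation indicates that the ideal number of participants per group is 10". The 3.22 is attributed to an earlier study of the same type of intervention and is treated as the smallest difference of substantial clinical relevance.

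The same section defends allocation by class on grounds of contamination and fixes the design at 12 children per class, with "3 experimental groups (6 class groups, n ± 72 children) and 3 control groups (6 class groups, n ± 72 children". Section 2.4 randomises the 12 classes within three educational levels.

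On the scale, section 2.9.1 says: "The domain scores can be transformed into a standard score (median = 10.0 and standard deviation = 3.0"). It also gives a raw total of 0 to 48, without an SD. Section 2.3 does not say which score the 3.22 and the 0.70 refer to.

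**The concern.** A difference of 3.22 against an SD of 0.70 is 4.6 standard deviations. So large an effect needs only a handful of children, so a requirement of 10 per group at 80% power cannot come from these figures. At least one input, or the result, is misstated.

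The calculation is also one for individually allocated children. Classes are the unit of allocation, and children in one class tend to resemble each other, yet no ICC or design effect is among the inputs.

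At stake is a stated property of the trial. The 80% is unsupported, and a reader cannot tell from section 2.3 what difference the trial can detect. That matters when a null result has to be interpreted.

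**Working it through.** **Inputs from section 2.3:** difference 3.22, SD 0.70, alpha 0.05, power 80%, loss 15%. Sidedness is not stated; two-sided is assumed.

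**1. Reproducing the stated figure**

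d = 3.22 / 0.70 = 4.60.

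Normal approximation: n = 2(1.96 + 0.842)² / 4.60² = 15.7 / 21.16 = 0.74, so 1 per group.

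Exact t test, noncentrality d·√(n/2), 2n − 2 df:

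| n per group | noncentrality | power |
|---|---|---|
| 2 | 4.60 | 0.661 |
| 3 | 5.63 | 0.983 |
| 10 | 10.29 | above 0.9999 |

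So 3 per group are needed. After loss: 3 / 0.85 = 3.5, so 4.

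Other set-ups do not reach 10 either: one-sided tests, power of 90 or 95%, alpha divided by 2, 3, 9 or 15, alpha of 0.001, paired tests, and ANOVA with 2, 4, 6 or 12 groups. The largest result was 6 after loss, at alpha 0.001.

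**2. What would give 10**

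- 80% power with 10 evaluable per group needs d = 1.325, so SD = 3.22 / 1.325 = 2.43.
- If 10 already includes loss, 8 are evaluable (8 / 0.85 = 9.4, so 10). Then d = 1.507 and SD = 3.22 / 1.507 = 2.14.

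**3. The design as fixed**

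There are 6 classes per arm and 12 × 0.85 = 10.2 children analysed per class. Class-level df = 12 classes − 2 arms − 2 for the three levels = 8. The ICC is not given; 0.05 to 0.20 is assumed.

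Design effect = 1 + (10.2 − 1)·ICC. Standard error in SD units = √(2 × design effect / (6 × 10.2)). The first set of results ignores the baseline measurement.

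| | ICC 0.05 | ICC 0.10 | ICC 0.20 |
|---|---|---|---|
| Design effect | 1.46 | 1.92 | 2.84 |
| Standard error (SD units) | 0.218 | 0.250 | 0.305 |
| Detectable at 80% power (SD units) | 0.70 | 0.80 | 0.98 |
| Power for 3.22 if SD 3.0 (d = 1.07) | 0.99 | 0.96 | 0.87 |
| Power for 3.22 if SD 5 (assumed) | 0.73 | 0.62 | 0.46 |
| Power for 3.22 if SD 6 (assumed) | 0.58 | 0.47 | 0.34 |

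SD 3.0 is the standard-score SD in section 2.9.1. SDs of 5 and 6 are assumptions for a raw score.

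Baseline adjustment with an assumed pre-post correlation of 0.7 multiplies the standard error by √(1 − 0.49) = 0.714. The detectable differences become about 0.50, 0.57 and 0.70 SD.

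**4. The meaning of the word group**

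The article uses it for the arm, for a level within an arm, and for a class. Since 10 / 0.85 = 11.8, which rounds up to 12, the 10 may be a per-class figure before loss. The inputs would still give 3. If a group is one level within an arm (2 against 2 classes, 2 df), power for 3.22 at SD 3.0 is only about 0.44 at ICC 0.01 and 0.22 at ICC 0.20.

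**The case against.** The best defence is that the slip does no harm. The protocol states more children than its inputs require, and 10 does not set enrolment: 12 per class and 144 in total are fixed separately. At SD 3.0 the detectable differences without baseline adjustment are about 2.1 to 2.9 points (0.70 × 3 to 0.98 × 3), below 3.22. This stands, and it rules out the inference that the trial has been shown to be underpowered.

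Three further readings are tempting but not supported.

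- **The SD of 0.70 contradicts the SD of 3.0 in section 2.9.1.** It does so only if 3.22 is a standard score. Section 2.3 names no scale, and no raw-score SD is given. The 0.70 looks very small and could be another statistic, such as a standard error or an SD of change. That calls for a query; it does not prove an error.
- **The 3.22 is an observed effect presented as a minimum relevant difference.** The Introduction does not report 3.22 for the cited study, so the documents do not show this. What they lack is a justification for the label.
- **The trial cannot detect a realistic effect.** The Introduction cites "locomotor skills (SMD = 0.44; 95% CI = 0.16 to 0.73") for teacher-led motor-skill programmes. Without baseline adjustment, power for 0.44 is about 43, 34 and 25% at ICC 0.05, 0.10 and 0.20. But that benchmark comes from programmes of 17 to 21 weeks that are not this intervention, and section 2.12 plans a group-by-time analysis that uses the baseline. With a pre-post correlation of 0.7 and baseline adjustment, the figures are about 70, 58 and 43%.

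An undisclosed design effect might lift 3 or 4 towards 10, but none is stated. None of this restores the stated result.

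**Conclusion.** Two things are wrong as written. The 10 per group at 80% power does not follow from the stated inputs: they give 3, or 4 after loss, and power of practically 100% at 10. And the calculation omits the clustering that its own section argues for, so the 80% does not describe 6 against 6 classes.

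The first conclusion rests only on figures printed in the article and holds under every variant tried. The size of the second depends on an ICC and an SD that the article does not give. Whether 144 children suffice for a 3.22 difference is therefore open: comfortably so at SD 3.0 over the ICC range shown, not so at an SD of 5 or 6 without baseline adjustment.

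**What to change.** Replace the 10 per group with a calculation for the design already fixed: 6 against 6 classes, 12 enrolled and about 10 analysed per class, two-sided 5%, class-level degrees of freedom, and an ICC range such as 0.05 to 0.20. In the same paragraph:

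- define the group to which the figure applies;
- name the score (raw or standard) for the 3.22 and the SD;
- check in the source what the 0.70 is, and use a between-child SD for the score to be analysed;
- state power or the detectable difference for the planned analysis that uses the baseline, with the assumed pre-post correlation. Without adjustment the detectable difference is about 0.70 to 0.98 SD; with adjustment it is smaller;
- justify 3.22 as a minimum relevant difference, or drop that label.

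The cost is one rewritten paragraph and possibly a less favourable stated power. This point calls for no extra children and no change to recruitment or intervention.

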### 2.4. Randomization and Blinding

The 12 class groups will be selected from 4 upper-middle-level classes (2 experimental and 2 control; age range between 3 and 4 years), 4 transition level 1 classes (2 experimental and 2 control; age range between 4 and 5 years) and 4 transition level 2 classes (2 experimental and 2 control; age range between 5 and 6 years), which will be randomized with stratified sampling [16]. This consists of segmenting the classes that agree to participate in the study according to educational levels (strata) and then performing a random sampling on each of them, using R statistical software, version 4.1.2. This study is considered double-blind because the measurements will be performed by professionals who are external to the research. 

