### 2.6. Intervention

The intervention will be implemented by early childhood educators, who will be trained about the objectives and contents of each session of CMSI that will be developed. Each session will take place in the classroom the preschoolers usually attend, which will depend on the admission policies of each educational community regarding the class levels (upper middle, transition level 1, and transition level 2). The intervention will last 12 weeks (36 sessions), distributed in 3 weekly sessions (Monday, Wednesday and Friday) of 40 min per session. CMSI is based on 2 previous studies [14,21], and a book related to CMSI [22]. Twelve unpublished motor stories will be distributed, one each week over 3 sessions, with the corresponding progressions for each session carried out. Thus, the children will be placed in a sequence of stories that begin with the presentation of a motivating character, who will accompany the children during the development of the whole story. The motor stories that will be developed each week are: (i) who I am; (ii) we go on an excursion; (iii) the school; (iv) the recess; (v) the weekend has arrived; (vi) visiting the park; (vii) my days in the field; (viii) my days at the beach; (ix) we go to the stadium; (x) we are going to know my environment; (xi) let’s go to the circus; (xii) tell me your adventures. The aim of the motor story translates into solving practical challenges while maintaining control, balance and coordination by combining various postures and movements such as throwing and receiving, moving on inclined planes and following rhythms, all in a variety of games and other activities [4,12,23].

The 40 min sessions will include three segments: (i) warm-up (5 min), which consists of joint mobility exercises and introduction to the motor story of the week; (ii) main part (25 min), which incorporates the narration of the motor story by the educator initially, as well as the participation of the children through their own corporeality with movements based mainly on FMSs (locomotion skills and object control), through two-way verbal interaction based on questions relating to the narration delivered by the educator or through direct verbal participation from each child; and (iii) cool down (10 min), where space is provided for the children to gradually return to calm, together with feedback on the content addressed during the session. Table 1 summarizes the materials and objectives of the weekly motor stories.

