### 2.7. Control Groups

The upper-middle-level control groups (n = 2 classes; n = 24 children), transition level 1 control groups (n = 2 classes; n = 24 children) and transition level 2 control groups (n = 2; n = 24 children) will participate in the assessments (initial and final) and will be asked to maintain their regular sessions at their educational establishments. At the end of the intervention period (according to the results obtained), the control group children, parents and/or legal guardians, managers and coordinators of each community will be contacted and provided with the material so that they can replicate the experience. In addition, the educators of these establishments (teachers and classroom assistants) will be trained in CMSI strategy.

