### 2.8. Outcomes and Procedures

The first meeting will be to obtain the agreement of the educational establishments and educators, to obtain the necessary signatures of informed consent and to explain the scope and aim of the study; also, the children will be randomly assigned to the intervention groups. During the following 2 weeks, the first assessments (pre-tests) will be carried out, before the 12-week CMSI is implemented; finally, the second assessments (post-tests) will be administered. One of the researchers will supervise all of the assessments and CMSI, and there will be a predefined order that will be followed by expert personnel in the assessments: (i) FMSs (physical education teacher specializing in early childhood care); (ii) language development (kindergarten teacher); (iii) physical activity level (physical education teacher); (iv) morphological variables (anthropometrist); and (v) sociodemographic variables (kindergarten teacher and physical education teacher). Figure 2 shows a summary of the assessments and sessions that are usually part of CMSI.

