#### 2.9.2. Language Development

The language test for preschoolers (TELEPRE) [29] will be used. The purpose of this assessment is to measure the language of children in initial educational levels (3 to 6 years old) by means of 4 domains: (i) language comprehension, (ii) language expression, (iii) vocabulary and (iv) language description. The administration of the instrument requires a booklet of questions, various objects (bottle, toy car, pencil, plate, needle, cup, paintbrush, screw, sponge, small ball, button, small book, spoon, scissors, matchbox; plus three objects that serve as distractors) and 3 pictures representative of situations (i.e., serving milk to a cat, setting the table and being in a toy store) to be described by the child. To administer the instrument, a room free from noise or other distraction is required, in which the evaluator, the child and a classroom assistant will be present. The estimated application time is ≤25 min. The test scores vary according to the domain and age of the child being evaluated; they are described in detail below, according to the original manual [29]. To interpret the scores, the original manual [29] proposes the use of T-scores (average = 50 points and standard deviation = 10). Regarding the validation of the instrument, its internal consistency varies between 0.87 and 0.93, according to the domain analyzed and a concurrent validity with the test of psychomotor development (TEPSI) [29].

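### The double-blind label in 2.1 and 2.4 is not supported: at most the outcome assessors can be blind, and that is neither stated nor protected

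*Protocol article*

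**What the plan says.** Section 2.1 of the protocol article sets the design: "The study is based on a double-blind, repeated measures and parallel groups". Section 2.4 gives the sole justification: "This study is considered double-blind because the measurements will be performed by professionals who are external to the research". Neither section says that these professionals are kept unaware of allocation, and neither names anyone else who is blinded.

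On delivery, section 2.6 states: "The intervention will be implemented by early childhood educators, who will be trained about the objectives and contents of each session of CMSI". Sessions take place in the children's usual classroom, three times a week for 12 weeks. On the comparator, section 2.7 says that control classes "will be asked to maintain their regular sessions at their educational establishments", and the Abstract puts it as "while the control groups will not receive any treatment". No sham or attention control is described.

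On measurement, section 2.8 states: "One of the researchers will supervise all of the assessments and CMSI". It assigns each test to a named type of professional and places random assignment at the first meeting, before the pre-tests. For the TELEPRE language test, section 2.9.2 describes a quiet room "in which the evaluator, the child and a classroom assistant will be present".

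**The concern.** The label and the reason given for it do not match. A double-blind claim tells the reader that at least two parties do not know the allocation, commonly the participants or those delivering treatment, and those assessing outcomes. The article's reason concerns only the assessors' independence from the research team.

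The TGMD-2 motor skills and the TELEPRE language domains are scored by a person watching or listening to a child. Knowledge of the arm can move such scores, usually in the direction the assessor expects. A reader who trusts the label will discount that bias. The Discussion gives no warning either: its limitations cover only adherence over the study period and sessions missed through illness or injury.

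**Working it through.** No calculation in the plan bears on this point, so the check sets the sections side by side, party by party, and then counts the outcomes exposed.

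**Who could be blind?**

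| Party | What the article says | Can they be blind? |
|---|---|---|
| Educators in CMSI classes | Trained in the content and deliver it (2.6) | No |
| Children | 12 weeks × 3 = 36 sessions of 40 min in their own classroom, against regular sessions (2.6, 2.7) | No: the arms differ visibly and there is no sham |
| Parents | Consent is sought with an explanation of scope and aim (2.8); control families are offered the material after the intervention period (2.7) | Not stated; blinding is not plausible with an untreated control |
| Researcher supervising CMSI | Also supervises all assessments (2.8) | No |
| Outcome assessors | External to the research (2.4) | Possible, but not stated |

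One party at most can be blind, so the design can be assessor-blinded but not double-blind.

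**Is assessor blinding secured?** Three features bear on it.

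1. Section 2.4 rests on assessors being external, yet section 2.8 puts a member of the research team over every assessment. That person also supervises CMSI and so knows which classes receive it. This is a direct route by which the arm could become known during testing.
2. Section 2.8 places assignment before the pre-tests. Allocation therefore exists at both measurement points, and what assessors are told matters at both.
3. A classroom assistant is in the room for the language test (2.9.2). Whether that person knows the arm is not stated.

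**Which outcomes are exposed?** Counting the primary variables named in the stated aim and in section 2.9:

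- TGMD-2: locomotor skills and object control = 2, observer-scored.
- TELEPRE: comprehension, expression, vocabulary and description = 4, observer-scored.
- Accelerometer: light activity, moderate-to-vigorous activity and sedentary behavior = 3, device-recorded.

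Total: 2 + 4 + 3 = 9. Observer-scored: 2 + 4 = 6, that is 6 of 9, or two of the three primary constructs.

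**The case against.** The best reply is that a condensed article need not describe how assessors are blinded, and that its silence does not show that they know the allocation. That stands. A reader might infer from 2.4 and 2.8 that no blinding exists at all, and the documents do not support this. External assessors may well be unaware of the arm. Section 2.8 has expert personnel carry out the tests in a set order, and nothing says that the supervisor scores or discloses anything. The overlap is a route of unmasking, not evidence that unmasking occurs.

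The same restraint applies to two other readings. The classroom assistant may know the arm, but the text does not say so, nor that the assistant scores or prompts. Section 2.8 also gives the language test to a kindergarten teacher, whom a reader might take for the class's own educator; section 2.4 says that those who measure are external.

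A reader might also want to express the possible bias as a share of the expected effect. The article gives no bias size, and the denominator is unsettled. The locomotor SMD of 0.44 in the Introduction comes from teacher-led motor-skill programs of 17 to 21 weeks, not from CMSI, while the planning values in 2.3 imply 3.22 / 0.70 = 4.6 SD. Any percentage would only restate an assumption.

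Condensation does not rescue the label itself. The article states both the label and the reason for it, and the reason does not lead to the label.

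**Conclusion.** The point holds for the label, with high confidence: sections 2.1 and 2.4 claim a property that the trial's own procedures rule out. That conclusion needs no assumption beyond the plain reading that those who deliver or attend CMSI know that they do.

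For assessor blinding the conclusion is weaker. It is not stated, and shared supervision puts it at risk, but it is not shown to be absent. This reaches six of the nine primary variables; the accelerometer variables are not scored by an observer and are not exposed in this way. The size of any resulting bias cannot be derived from the document. The lack of blinding among educators and children is unavoidable in a trial of this kind and is not the criticism. The label and the overlap in supervision are avoidable.

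**What to change.** 1. In 2.1 and 2.4, replace double-blind with: assessor-blinded; educators, children and parents not blinded.
2. State in 2.4 that the motor-skill and language assessors are not told which classes receive CMSI, at pre-test or post-test. The concealment has to work at class level. Whole classes are allocated, so coding individual children's names would do little.
3. In 2.8, have a team member who did not supervise CMSI oversee the post-tests. If none is available, report the overlap as a limitation in the Discussion.
4. Tell classroom staff, including the assistant present at the language test, not to disclose the arm.

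Recording each assessor's guess of the arm at post-test is optional.

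The cost is a less favourable label and a small change to the supervision roster. The article does not give the size of the team, so it cannot be confirmed that a separate supervisor is available; the fallback in item 3 covers that case. No extra children, visits or instruments are needed.
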